### Data and safety monitoring

The patients will be reviewed on the ward post caesarean section for any signs of complications until discharge. The patients will be given a phone number to call to contact the investigator in case of any reaction and complication in relation to the caesarean section scar. Advice will be given to patients over the phone, or they will be invited to present to hospital for review for further management.

There will be an independent data and safety monitoring committee, including assessors independent of the Department of Women’s and Newborn Health, who will review all data and conduct audits of the trial at intervals to assess the safety and critical efficacy of the intervention, disentangle harms of corticosteroids from surgical complications and accordingly decide whether to continue, modify or stop the clinical trial.

### Interim analysis

An interim analysis will be performed on the primary outcome of keloid formation in patients when enrolling 20 patients, including both the control and intervention groups, by a single statistician who is blinded to allocation and reports the results to the data and safety monitoring committee.

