### Follow-up

The follow-up period consists of 12 months face-to-face visits (Fig. 1). Post-operation, the patients will be visited daily on the ward for any signs of potential infectious local complications of the treatment and immediate side effects of the medication injection until the discharge home. The patients will then be visited in the women’s health clinic at the hospital for their 6th week post-partum check. The next follow-up times will be 6 months and 12 months post caesarean section. At each follow-up visit, the same assessment and scoring scales will be used to evaluate the changes to the keloid scar. Late side effects of the medication injection as well as symptoms of depression, anxiety and stress, and participants’ satisfaction will be assessed during follow-up visits at 6 weeks, 6 months and 12 months post-partum. The participants will also be asked if they would recommend such a procedure to another woman with a caesarean section keloid scar (yes/no) and if they would repeat the experience again in a future pregnancy (yes/no).

All measurements at baseline and follow-up visits will be performed by the same researcher, who will also make all efforts to ensure compliance with follow-up. As part of continuous clinical care, patients with any residue keloid scar with be given information on further treatment including referral to plastic surgeons if they are interested (Fig. 2).

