### Data analysis

Intention-to-treat analysis will be performed using SPSS Advanced Statistics version 24.0 (SPSS, Chicago, IL, USA). Descriptive statistics will be used to summarise the demographic data; binary outcomes will be summarised with a relative risk (RR) and 95% confidence intervals (CIs) and compared between the two groups using a χ^2^ test (or Fisher’s exact test where applicable). Comparison of the number of patients with keloid formations within groups and between the two groups will be done using a χ^2^ test. A *t* test will be used to assess continuous non-skewed variables; these will be presented as means with standard deviations. For skewed ordinal data, the Mann–Whitney *U* test will be used; these data will be presented as medians with interquartile ranges. Difference in the effect over the sub-groups will be assessed using logistic regression. Outcomes of interest will be number of patients with keloid formation, changes in the appearance and specification of the keloid scar, depression, anxiety, stress and patient’s satisfaction. Changes in the appearance and specification of the keloid scar after the intervention will be summarised into two groups (binary outcome: 0 = changed, 1 = not changed) and will be analysed using logistic regression adjusting for the number of keloids formed and demographic variables. A *p* < 0.05 will be considered statistically significant.

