### Trial status

The present protocol is version number 4, dated October 2018. The recruitment began in May 2019 and is expected to complete by June 2021.

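### The interim analysis of keloid formation is triggered by enrolment of 20 women, before any 6- or 12-month outcome is likely to exist, yet it feeds a decision that may rest on efficacy

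*Protocol article*

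**What the plan says.** The Interim analysis section of the protocol article states: "An interim analysis will be performed on the primary outcome of keloid formation in patients when enrolling 20 patients". It covers both arms and is carried out "by a single statistician who is blinded to allocation and reports the results to the data and safety monitoring committee". No visit is named at which keloid formation is to be read.

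Under Data and safety monitoring, the committee is to "conduct audits of the trial at intervals to assess the safety and critical efficacy of the intervention" and "accordingly decide whether to continue, modify or stop the clinical trial".

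The Procedures section places recruitment and randomisation at around 36 weeks of gestation, before the caesarean section. Under Follow-up, the scar is reassessed at the 6-week check, and then: "The next follow-up times will be 6 months and 12 months post caesarean section". Trial status says: "The recruitment began in May 2019 and is expected to complete by June 2021".

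Data analysis gives one significance level, p < 0.05. The Sample size section uses a two-sided 5% level.

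**The concern.** The trigger counts women enrolled, not women assessed. Enrolment precedes surgery, and the later scar assessments come 6 and 12 months after it, so a look at the 20th enrolment falls before most of the outcome it is meant to analyse can be observed. The committee that receives the result may consider efficacy and may stop or change the trial.

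There are two ways to carry out the sentence, and only one can apply:

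- **At the 20th enrolment.** The look rests on a handful of 6-week assessments.
- **Once the 20 women have outcomes.** The look compares about 10 with 10. That has little power, and any significant result must show an effect much larger than the one the trial assumes. If that result can support an efficacy claim at 0.05, false-positive risk is added to the final test.

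Either way, a trial of 150 women could be stopped or reshaped on weak evidence.

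**Working it through.** **Inputs.** Sample size: 150 women, 75 per arm, 45% v 70%, 80% power, two-sided 5%, 10% non-compliance. Randomisation: 1:1 in blocks of 10, so 20 women are two full blocks, 10 v 10. Trial status: May 2019 to June 2021, about 25 months (24 to 26). Assumptions not in the document: even accrual, and 2 to 4 weeks from consent to surgery.

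**The plan's own figure.** The two-proportion formula with continuity correction gives 68 per arm. 68 × 1.1 = 74.8, so 75 per arm and 150 in total. The stated size reproduces.

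**Timing.**

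- Rate: 150 / 25 = 6 per month. The 20th woman enrols at 20 / 6 = 3.3 months (3.2 to 3.5 for 26 to 24 months' uncertainty in the accrual period).
- Woman *i* then has follow-up of (20 − *i*)/6 months minus the gap to surgery. With a 3-week gap (0.69 months), 15 of the 20 have been operated on.
- Six weeks is 1.38 months. A 6-week visit needs (20 − *i*)/6 ≥ 0.69 + 1.38, so *i* ≤ 7: seven women.
- Over gaps of 2 to 4 weeks and accrual periods of 24 to 26 months: 14 to 17 operated on, 5 to 9 past 6 weeks, none at 6 or 12 months. The longest follow-up is 2.1 to 2.8 months.
- For one woman to have a 6-month outcome, accrual must be below 19 / (6 + 0.69) = 2.8 per month. For a 12-month outcome it must be below 19 / (12 + 0.69) = 1.5 per month.

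**Power if the look waits for outcomes in 20 women.** Enumerating all binomial results for 10 v 10 at 45% and 70%:

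| Interim test at 0.05 | Power | Rejection when both arms are 45% |
|---|---|---|
| Pearson chi-square, uncorrected | 18.1% | 4.2% |
| Fisher's exact | 8.3% | 1.3% |

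The smallest difference that reaches p < 0.05 by chi-square is 4 of 10, and only at the extremes. For 0 v 4, z = 0.40 / √(0.2 × 0.8 × 2/10) = 2.24, which is significant. For 1 v 5, z = 0.40 / √(0.3 × 0.7 × 2/10) = 1.95, which is not. So significance needs at least 40 points, against 25 assumed: 40 / 25 = 1.6 times the design effect.

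**Type I error if that look is a between-arm test at 0.05 that can stop for efficacy, with the final test also at 0.05.**

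- Normal approximation: correlation √(20/150) = 0.365, both boundaries 1.96, overall 9.4%.
- Exact enumeration with both arms at 45% and a final chi-square on 75 per arm:

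| Analysis | Overall type I error |
|---|---|
| Final test alone | 5.6% |
| With Fisher interim | 6.7% |
| With chi-square interim | 9.2% |

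On the exact scale the look therefore adds 1.1 to 3.6 points.

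**Check of the remedy.** At information fraction 20/150, p < 0.001 at the look and 0.05 at the end give 5.08% overall. A final level of 0.0492 brings it to 5%.

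**The case against.** A reader might infer that the trial has no error control at all. The document does not support that. It is a journal article, and a stopping boundary is commonly left to an analysis plan or a committee charter, neither of which is shown. Nor does the Interim analysis section say that 0.05 is its threshold; that level comes from the general statement under Data analysis. The statistician is blinded to allocation, so a pooled look, which adds no type I error, is possible, as are coded arms. The error figures are therefore conditional.

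A reader might also take 9.4% as the cost of the design. It is the top of a range, it depends on the test used, and it cannot apply together with the complaint that data are missing: a look at the 20th enrolment does not have outcomes on 20 women.

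It would also be too strong to say that the look would have no data. The same scales are used at 6 weeks, and the primary outcome is not restricted to later visits, so such a look would be thin but not empty. The timing assumes even accrual, and the trigger could be read loosely as the first 20 women once assessed.

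What remains is the stated trigger. It names enrolment and no visit, for an outcome that follows surgery, and nothing in the text limits the look to safety, futility or pooled data. Accrual would have to run at less than half the implied pace before a single 6-month outcome existed.

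**Conclusion.** The concern holds for the trigger and for the decision attached to it. As written, with even accrual and 2 to 4 weeks from consent to surgery, the look falls at about 3.3 months, with no 6- or 12-month outcomes and 6-week data on about 5 to 9 of 20 women. The committee may still "assess the safety and critical efficacy of the intervention" and act on the result.

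If the look is delayed until these 20 women have outcomes, power is 8% to 18%, and a chi-square result is significant only if the observed difference is at least 40 points. Overall type I error of about 6.7% (Fisher interim) to 9.2–9.4% (chi-square interim or normal approximation) applies only if that delayed look is a between-arm test at 0.05 that can stop for efficacy, and only if no boundary is set elsewhere. The trigger needs correction even if such a boundary exists.

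**What to change.** In the Interim analysis section, make this look safety-only and trigger it when the 20th participant completes the 6-week visit, with adverse events and wound complications reviewed by arm and no between-arm test of keloid formation. Under Data and safety monitoring, limit the committee's decision at this look to safety.

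If an efficacy look is kept, tie it to completed 12-month outcomes, allow an efficacy claim only at p < 0.001, and set the final level at about 0.049. Leaving the final level at 0.05 gives 5.08% overall. With 20 women this fallback would almost never stop the trial: under 45% v 70%, p < 0.001 is reached with probability of about 0.4% (Fisher) to 0.6% (chi-square). With even accrual and 3 weeks to surgery, about 93 to 96 women would already be enrolled when the 20th reaches 12 months.

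The cost is a few sentences in the protocol and a matching entry in any committee charter, with no added patients. The downside is the loss of an early efficacy stop at 20 patients, where power was negligible.

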### Harms

If there is a reasonable suspected causal relationship with the intervention, the study researcher who is blinded to the allocations will report to the data and safety monitoring committee, who will in turn report the adverse events to the ethics committee to guarantee the safety of the patients. We do not expect any risks for either group (control or intervention).

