Based on the cellular mechanism of keloid formation, one of the first-line options to treat keloid scars is corticosteroid injection into the affected area. The steroids have both direct anti-inflammatory and vasoconstrictive effects. Administration of corticosteroids results in the whitening of keloid scars, suggesting a decrease of blood flow in the scar due to vasoconstriction [7].

Another suggested treatment of keloid scars is surgical removal of the scar. However, since surgical removal of the keloid usually only provides temporary cosmetic relief and invariability followed by even more aggressive regrowth of scar tissue in 50–100% of cases, many clinicians perform surgical excision of the keloid scar followed by sub-dermal corticosteroid injections. This has been suggested to be effective for patients with small or single site lesions [9].

Some studies have used immediate wound edge corticosteroid injection after the excision in patients with hypertrophic scars and keloid scars, followed by regular injection of corticosteroid: usually a weekly injection for 2–5 weeks followed by monthly injections for 3–6 months [10]. This combination of surgical removal and corticosteroid injections has been shown to improve outcome. This dose of steroid is substantially more than the stat dose we plan to use in our study and requires multiple visits and repeated injections.

A thorough literature search has shown a lack of research on the surgical excision and injection of corticosteroid injection immediately after the excision of the existing caesarean section keloid scars. Therefore, in the proposed study, we aim to investigate the effect of corticosteroid (triamcinolone acetonide) injection immediately after surgical removal of old caesarean section keloid scars on the recurrence of the scars.

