### Procedures

All eligible women will be approached at the time of booking into the clinic for caesarean section at around 36 weeks and will be given information about the study. Those women who meet the inclusion criteria and sign the informed consent form will be randomised to either the intervention or the control group by the independent researcher as explained previously (Fig. 1). On the day of the caesarean section, the sealed envelope containing instructions for the type of treatment will be picked up by the surgeon. The surgeon opens the envelope when the woman is ready for the caesarean section.

The control group will receive surgical excision of the keloid scar at the beginning of the procedure during skin incision. The baby will be delivered as normal, and routine wound closure will be performed in accordance with National Institute for Health and Care Excellence (NICE) guidelines as follows: The uterus is closed in two layers followed by closure of the rectus sheath, all using continuous sutures with 1-Vicryl (Johnson & Johnson). The fat layer is closed with interrupted plain gut sutures 2 cm apart. The skin layer is then closed with 3-0 Monocryl (Ethicon) in a sub-cuticular fashion.

The intervention group will receive surgical excision of the keloid scar after the delivery of the baby. Closure of the uterus layers, rectus sheath and the fat layer are completed as explained above. Then, triamcinolone acetone will be injected sub-dermally at the time of wound closure. Two ampules of triamcinolone acetonide (Kenacort®-A 10 suspension, Aspen Pharma Pty Ltd) will be administered at a single dose; each ampule contains 10 mg/1 ml active medication. The surgeon will inject one ampule along the entire length of the upper edge of the skin incision and one ampule along the entire length of the lower edge of the skin incision, using a 25 G needle.

After the procedure is completed, the surgeon will fill in the post-operation survey. The excision of the scar and administration of the injection will be performed by the surgeon who is scheduled to perform the surgery on that day. All the surgeons in the Department of Women’s and Newborn Health will be trained on how to perform the excision and injection of the triamcinolone. The Principal Investigator of the study will assess the fidelity to the intervention by supervising procedures.

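### The Harms section expects no risk in either arm, which contradicts the protocol's own text on regrowth after excision and on triamcinolone, and the binary scar summaries do not separate a worse scar from a better one

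*Protocol article*

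**What the plan says.** All references are to the protocol article.

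- **Harms:** "We do not expect any risks for either group (control or intervention". Reports to the monitoring committee begin "If there is a reasonable suspected causal relationship with the intervention".
- **Background:** removal of a keloid usually brings only temporary relief and is "followed by even more aggressive regrowth of scar tissue in 50–100% of cases". This is given as the reason many clinicians add corticosteroid.
- **Procedures:** "The control group will receive surgical excision of the keloid scar at the beginning of the procedure during skin incision". Delivery and routine closure follow, with no injection.
- **Discussion:** hypopigmentation, atrophy and telangiectasia are named as common adverse effects of triamcinolone, and the local infection risk is expected to be minimal.
- **Follow-up:** ward visits look for "any signs of potential infectious local complications of the treatment and immediate side effects of the medication injection until the discharge home". Later visits assess "Late side effects of the medication injection as well as symptoms of depression, anxiety and stress", and the scar is re-measured at 6 weeks, 6 months and 12 months.
- **Data analysis:** the number of women with keloid formation is compared within and between groups. Change in the scar is reduced to a binary variable, with changed coded 0 and not changed coded 1.

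**The concern.** A Harms section that expects no risk cannot stand beside a Background that attributes aggressive regrowth to the procedure given to the whole control arm, nor beside a Discussion that lists common effects of the study drug. The statement is about safety, so readers will take it as the protocol's position on what participants face.

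The second part concerns what the analysis can show. Both arms are excised. A difference in favour of triamcinolone could appear while an unknown number of women in either arm finish with a larger scar than they brought to the trial. The two binary summaries that the protocol states would not reveal that number.

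**Working it through.** **1. Size of the control arm.** The Sample size section gives 75 per arm for 45% versus 70%, 80% power, two-sided 5%, with 10% allowed for non-compliance. This figure is not disputed and is used only for the control-arm count. To reproduce it:

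- n = [1.96·√(2·0.575·0.425) + 0.842·√(0.45·0.55 + 0.70·0.30)]² / 0.25² = 60.2, so 61 per arm.
- With continuity correction: (60.2/4)·[1 + √(1 + 4/(60.2·0.25))]² = 68 per arm.
- With the 10% allowance: 68/0.9 = 75.6, so 76; or 68·1.1 = 74.8, so 75.

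The stated 75 per arm is reproduced with the continuity correction.

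**2. Regrowth implied for controls.** Background rate 50% to 100%, applied to 75 women:

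- 75 × 0.50 = 37.5, about 38
- 75 × 1.00 = 75

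If 10% were not evaluable (an assumption; the protocol's 10% is for non-compliance), about 67 remain: 67 × 0.50 = 33.5, about 34, up to 67.

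These counts are for regrowth of any extent. The protocol gives no rate for regrowth beyond the original size.

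**3. The statements side by side.**

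| Arm | Harms | Elsewhere in the article |
|---|---|---|
| Control | no risk expected | regrowth in 50% to 100% after excision (Background) |
| Intervention | no risk expected | common drug effects; infection risk minimal but not nil (Discussion) |

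The sentence conflicts with the rest of the article in both rows.

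**4. What the binary summaries can show.** A keloid at entry is an inclusion criterion, so the proportion with a keloid starts at 100% in each arm. It can stay there or fall; it cannot register deterioration. Consider four possible results at 12 months:

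| Result | Keloid formation | Change code |
|---|---|---|
| No keloid | no | 0 (changed) |
| Keloid, smaller than baseline | yes | 0 (changed) |
| Keloid, as at baseline | yes | 1 (not changed) |
| Keloid, larger than baseline | yes | 0 (changed) |

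The second and fourth rows are identical on both variables, so a woman who improved and a woman who worsened cannot be told apart. The t test or Mann–Whitney test on the measurements could show an average shift, but not how many women ended worse.

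**The case against.** The strongest reply is that regrowth is anything but ignored. It is the primary outcome in both arms, measured by caliper and photographed against baseline at every follow-up visit. The interim analysis of keloid formation goes to the committee. The Data and safety monitoring section gives women a telephone number for complications of the scar, and has the committee review all data and separate corticosteroid harms from surgical ones. The secondary objectives include side effects of excision together with injection. Counting recurrence as lack of efficacy, not as an adverse event, is a common convention. All of this stands. A reader might infer from the Harms and Follow-up wording that regrowth in a control woman reaches no monitoring route at all; the documents do not support that.

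Three further inferences also go too far.

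- **That excision is shown to do harm if scars exceed baseline.** Every participant has a repeat caesarean, and the Background says surgery itself can trigger keloid in predisposed people. With no unexcised arm, own-baseline comparison describes worsening but does not attribute it.
- **That the planning rate gives a control failure count.** The 45% comes from excision followed by radiation, so it is not an excision-only rate.
- **That participants are misinformed.** The participant information is not shown, and nothing can be concluded about it.

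It could also be said that the Harms sentence means no risk beyond ordinary care. The sentence carries no such limit. Procedures describes the closure as routine but does not say so of the excision, for which surgeons are to be trained.

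**Conclusion.** The point holds in limited form. The no-risk expectation contradicts the Background for the control arm and the Discussion for the intervention arm, and these sections must be reconciled. On the Background figure, about 38 to 75 of 75 controls would have regrowth. That assumes a rate quoted for keloid excision in general carries over to caesarean scars, which the article does not say.

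A reader might take the Background's phrase as meaning that most controls will end with a keloid larger than the one removed. That is an interpretation: the article gives no size relative to the original and no rate for exceeding it. The extent of worsening is therefore unknown. The stated binary summaries would not make it known, although the measurements needed are already planned.

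**What to change.** 1. In Harms, replace the no-risk sentence with the risks the protocol itself gives: regrowth after excision as in the Background, and the drug effects and infection risk as in the Discussion.
2. Add a descriptive safety summary: by arm, at 6 and 12 months, the number and proportion of women whose scar is larger than at their own baseline. Fix beforehand which dimension or dimensions count and what increase counts as larger; the caliper reads to 0.02 mm, so without a margin any trivial increase would qualify.
3. Include this summary in the data sent to the monitoring committee.
4. State beside the table that it describes worsening and cannot attribute it to excision, since all women also have a repeat caesarean. Baseline is also taken in pregnancy and follow-up after delivery, which may affect the dimensions.

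The cost is a less favourable risk statement and one extra table. Visits, measurements, sample size and treatment are unchanged.
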